## Discussion

The treatment of Parkinson’s disease has attracted increased attention from doctors and researchers in recent years. Although dopaminergic drug therapy is effective for controlling motor symptoms, side effects and motor complications are often induced by taking these medicines [13, 14]. Therefore, combining alternative therapies may be helpful to solve these problems. Moxibustion, as a traditional Chinese medical therapy, is beneficial for ameliorating motor and nonmotor symptoms to some extent based on clinical observations. However, high-quality trials and evidence concerning the efficacy of moxibustion for treating PD are still lacking. The objective of this trial is to confirm the effectiveness and safety of moxibustion in patients with PD and provide evidence for physicians to better improve clinical effectiveness in treating PD.

In this study, we selected the early stage of PD as our research objective because our previous preclinical studies indicated that moxibustion was effective for reducing the death of dopaminergic neurons and improving motor behavior in the early stage of PD [9, 10]. From the point of view of the clinic, the earlier the moxibustion intervention is implemented, the better the effect will be. The later stage of PD is always accompanied by severe damage and loss of dopamine neurons, and any intervention in this stage will be hard to remedy and attain satisfactory symptomatic control [15]. Therefore, to obtain a better clinical effect and observe significant group differences, we only included patients with early-stage PD.

The acupoints we will choose in these trials are DU20 and EX-HN1. Stimulating DU20 is vital to connect different parts of the brain and regulate brain function [16]. Previous reviews concerning acupoint selection for treating Parkinson's disease also demonstrated that DU 20 has been frequently applied in PD and is vital for alleviating PD symptoms [17, 18]. Our previous animal studies suggested that moxibustion at DU20 suppresses 6-OHDA-induced nigrostriatal dopaminergic cell death in a rat PD model [9, 10]. Other studies also indicated that stimulating DU20 protected dopaminergic neuronal cells from further injury and could modulate the cerebello-thalamo-cortical circuit to control PD tremor symptoms [19, 20]. EX-HN1 is located around DU20, which has a similar effect as DU20. In addition, combining EX-HN1 and DU20 will strengthen the synergistic effect for treating PD based on the theory of traditional Chinese medicine. Previous studies also suggested that moxibustion at EX-HN1 and DU 20 could protect dopamine neurons and reduce oxidative stress injury of the nigrostriatal system in rats with Parkinson's disease [21]. Therefore, we selected DU20 and EX-HN1 as our moxibustion acupoints.

Because moxibustion is a nonmedical therapy, it is difficult to apply the blinding method. The therapeutic function of moxibustion mainly contributes to the moxa material and heat stimulation. Previous methods commonly control one factor (used a base of the sham pillar or kept a far distance from the acupoints to isolate the heat stimulation) as sham moxibustion intervention [22, 23]. Another study only used nonmoxa material for sham moxification [24]. Most of these previous methods of sham moxibustion could only control one moxibustion effect factor. In this trial, we will try to control both heat and material factors that play a role in moxibustion. We set the distance of placebo moxibustion to 8-10 cm and kept a constant temperature at 37 °C, which will minimize heat stimulation and make participants feel warm, thereby creating a blinding effect [25, 26]. We also used Artemisia argyi as the sham material moxa, which might not have any treatment effect based on previous studies [24]. The sham moxibustion will maintain the same appearance as the moxa stick, and this method will make it difficult for the participants to distinguish the sham control or true moxibustion that will help to blind the participants. However, the blinding of the practitioners will be difficult to achieve because the smell, smoke and distance of the sham stick are different from those of the true moxibustion group. A third independent assessment of the treatment effect will help to overcome this limitation.

In this trial, we will estimate the overall effect of moxibustion on motor function and nonmotor function in PD to better understand and confirm the treatment effect of moxibustion in PD. In addition, we also explored the potential mechanism by which moxibustion regulates PD, which mainly involves the iron metabolism indicators that we verified in preclinical experiments [9, 10]. Previous studies also indicated that the pathogenetic mechanism of PD might be related to the ferroptosis of dopaminergic neurons [27, 28]. Therefore, we explored the potential mechanism of moxibustion in PD based on the ferroptosis mechanism in this trial. In addition, we will compare the BOLD signal changes in different brain areas using fMRI between the moxibustion and sham moxibustion groups to locate and quantify specific brain functional area changes. We attempted to directly observe the regulatory effect of moxibustion on the brain function of Parkinson's disease patients.

However, there are still limitations to this trial. First, although we tried to improve the blinding method in this protocol, due to the nature of moxibustion, genuine blinding of practitioners is difficult to achieve. This may have introduced performance bias and detection bias to an extent. Second, our study is only a single-center trial in one hospital in China, and whether these results may be able to generalize significance and applicable for other patients in other areas is still unclear.

In conclusion, the results of this trial will answer whether moxibustion is effective for treating PD in motor and nonmotor symptoms and provide a reliable and evidence-based protocol as an alternative selection for physicians to treat PD. This trial will also preliminarily explore the potential mechanism of the regulatory effect of moxibustion in PD, which will contribute to providing a theoretical basis for the treatment of PD.

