**Discussion:**

In conclusion, the results of this trial will reveal whether moxibustion is effective for treating motor and nonmotor symptoms in PD. This trial will also preliminarily explore the underlying mechanism of the regulatory effect of moxibustion in PD, which will contribute to providing a theoretical basis for the treatment of PD.

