### Outcome measures

The mean change in MDS-UPDRS scores (including MDS-UPDRS II, part III subscale, total score) from baseline to the observation points will be the primary outcomes. Scores on the Parkinson’s Disease Questionnaire-39 (PDQ-39), Fatigue Severity Scale (FSS), Parkinson Disease Sleep Scale (PDSS), Montreal Cognitive Assessment (MoCA), and Self-Rating Depression Scale (SDS) as well as the Wexner constipation score will be regarded as secondary outcomes and will be assessed at 4 and 8 weeks. All initial assessments will be followed up at week 16.

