### Statistical analysis

Statistical analysis of the data will be conducted by researchers blinded to group assignments using SPSS (version 25). Intention-to-treat analysis will be performed for all assigned participants. The missing data will be imputed by the last observation carried forward (LOCF) method. All included data will be first tested to determine whether they meet the normality test. If data conformed to a normal distribution, the mean ± standard deviation will be used. Otherwise, data will be expressed as M (P25-P75). An unpaired t test will be used when the data meet a normal distribution; otherwise, a nonparametric test (Mann–Whitney U) will be used to analyze comparisons between the moxibustion group and the control group. A P value less than 0.05 will be considered statistically significant.

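### The article promises an answer on nonmotor efficacy, but the nonmotor scales are only secondary outcomes, tested at an unadjusted 0.05 over several visits with none named as decisive

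*Protocol article*

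**What the plan says.** Three statements set out what the trial is meant to conclude. The abstract says "the results of this trial will reveal whether moxibustion is effective for treating motor and nonmotor symptoms in PD". The closing paragraph of the Discussion says "the results of this trial will answer whether moxibustion is effective for treating PD in motor and nonmotor symptoms". Earlier in the Discussion the article says "we will estimate the overall effect of moxibustion on motor function and nonmotor function in PD to better understand and confirm the treatment effect". Tentative wording about exploring is kept for the mechanism work, that is, the blood tests and fMRI.

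Under Outcome measures, the upper tier is set as follows: "The mean change in MDS-UPDRS scores (including MDS-UPDRS II, part III subscale, total score) from baseline to the observation points will be the primary outcomes". The PDQ-39, FSS, PDSS, MoCA, SDS and Wexner score form the lower tier; they "will be regarded as secondary outcomes and will be assessed at 4 and 8 weeks. All initial assessments will be followed up at week 16".

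Under Statistical analysis, groups are compared by an unpaired t test or Mann-Whitney U test, and "A P value less than 0.05 will be considered statistically significant". No adjustment, testing order, key secondary outcome or decisive secondary visit is stated.

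**The concern.** The promised conclusion and the stated means of reaching it do not match. Motor and nonmotor efficacy stand side by side in the conclusion, but the scales that measure nonmotor symptoms directly sit only in the secondary tier. The one decision rule given treats each scale at each visit alike.

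Unadjusted secondary tests are common and harmless when they are read as supportive. Here they would have to carry part of the main conclusion. Nothing in the article stops an isolated result below 0.05, on one scale at one visit, from being reported as the promised nonmotor answer, even if the MDS-UPDRS comparison fails. Settling which MDS-UPDRS score and visit is decisive would not help, because the nonmotor scales form a separate set of tests.

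**Working it through.** **The plan's own figures.** The article gives no error rate for the secondary outcomes, so there is none to reproduce. Its sample size does reproduce from its own formula: 2 × (1.96 + 0.842)² × 0.783 × 0.217 / 0.30² ≈ 29.6, and 29.6 / 0.85 ≈ 34.9, hence 35 per group. What matters here is the 1.96. It shows that the 0.05 is two-sided, so the nominal chance of a false result favouring moxibustion is 0.025 per test.

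**Inputs from the article.**
- Dedicated nonmotor scales: 5 (FSS, PDSS, MoCA, SDS, Wexner). The PDQ-39 is a general disease questionnaire and is left out of the main count.
- Visits: weeks 4 and 8 during treatment, and week 16 at follow-up.
- Tests: 5 at one visit, 5 × 2 = 10 over weeks 4 and 8, 5 × 3 = 15 over all three.
- Rule: two-sided P < 0.05 for each test, unadjusted.

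**Assumptions not in the article.** There is no true effect on any of the scales. Each test statistic is standard normal, with scales oriented so that positive favours moxibustion. The correlation is 0.5 between scales and 0.7 between visits of one scale (the product of the two for different scales at different visits). Between-scale values from 0 to 0.7 and between-visit values from 0.5 to 0.85 are shown as a range.

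**Upper reference, independent tests.** The chance of at least one false result favouring moxibustion is 1 − 0.975^k:
- k = 5: 11.9%
- k = 10: 22.4%
- k = 15: 31.6%

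**With correlation.** The quantity is the probability that at least one Z exceeds 1.96 (favouring moxibustion) or that at least one |Z| exceeds 1.96 (either direction). It was obtained by simulation, with at least 200,000 draws per setting.

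| Five scales | Favouring moxibustion, central | Range | Either direction, central |
|---|---|---|---|
| One visit | 9% | 7-12% | 18% |
| Weeks 4 and 8 | 14% | 11-21% | 29% |
| Weeks 4, 8 and 16 | 18% | 13-28% | 36% |

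The nominal levels are 2.5% favouring moxibustion and 5% in either direction. The low end of each range has strong correlation and the high end has uncorrelated scales.

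**Sensitivity to the PDQ-39.** With six scales and the same central correlations, the figures favouring moxibustion are about 10%, 16% and 21%. In either direction they are about 21%, 32% and 40%.

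**The case against.** The strongest reply is that this is a condensed article. Multiplicity for secondary outcomes, a key secondary and a testing order usually belong in a statistical analysis plan, which may exist. That stands: the missing adjustment alone is not a fault. What remains is a published conclusion set beside a published blanket rule. An analysis plan that called these scales exploratory would be at odds with the abstract and the Discussion.

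Second, the error rates belong to a rule that the article never states. A reader might infer that one significant scale at one visit counts as nonmotor efficacy. The Statistical analysis section defines only when a comparison is called significant, and the Discussion speaks of an overall effect. The figures are therefore conditional on that reading, which the text neither adopts nor rules out.

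Third, a reader might quote a 20-40% chance of a false nonmotor finding. That figure counts results favouring sham and includes the PDQ-39. For a false claim of benefit on the five dedicated scales, the central figures are 9-18%.

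Fourth, it would be wrong to say that there is no hierarchy, or that every outcome not called exploratory is confirmatory. The article does separate primary from secondary outcomes. Nor does it say which outcomes decide the nonmotor question. The MDS-UPDRS total is primary, but the article draws no separate nonmotor result from it.

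Finally, carrying the last observation forward brings visits closer together and lowers the multi-visit figures. The between-visit range up to 0.85 gives some allowance for this.

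**Conclusion.** The point holds as a mismatch between the promised conclusion and the status and testing of the outcomes behind it. The article says it will reveal, confirm and answer whether moxibustion works for nonmotor symptoms, while the scales that measure them are secondary, repeated over up to three visits and judged by one unadjusted 0.05 rule, with no scale or visit decisive.

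If any single favourable result were accepted as the answer, the chance of a false claim of benefit would be roughly three to seven times the nominal 2.5% at the central correlations (9 / 2.5 ≈ 3.6 for one visit, 18 / 2.5 ≈ 7.2 for three). Even the lowest figure in the range, 7%, is nearly three times nominal. The size rests on assumed correlations and on that conditional reading; the mismatch does not. The primary analysis and the sample size are untouched. The point is worth correcting because it changes what the trial may conclude.

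**What to change.** Under Outcome measures and Statistical analysis, state that the secondary scales are supportive or exploratory, and that they will be reported as between-group differences with 95% confidence intervals and without a claim of proven nonmotor efficacy. Reword the abstract's Discussion paragraph and the two Discussion statements so that the trial answers the primary MDS-UPDRS question and explores nonmotor symptoms.

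Only if the sponsor wishes to keep a nonmotor claim: fix one visit in advance and test the scales by a multiplicity procedure such as Holm, after a significant primary result. The smallest P value would then have to fall below 0.05 / 5 = 0.01 for the five scales, or 0.05 / 6 ≈ 0.0083 if the PDQ-39 is included. This is an option on which statisticians could differ. Fixing a visit without adjusting still leaves about 9% against 2.5%.

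The cost is a few sentences, with no new data or patients. The downside is that an isolated significant secondary scale can no longer be presented as proof of nonmotor efficacy.

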## Trial status

This trial is currently in the recruitment phase. Patient recruitment started in October 2021 and is expected to finish at the end of 2023.

## Data Availability

The original contributions presented in the study are included in the article/Supplementary Material, further inquiries can be directed to the corresponding author/s.

## Abbreviations

PD: Parkinson’s disease
DU20: Baihui
EX-HN1: Sishenchong
PDQ-39: Parkinson’s disease questionnaire-39
FSS: Fatigue severity scale
PDSS: Parkinson disease sleep scale
MoCA: Montreal cognitive assessment
SDS: Self-rating depression scale
fMRI: Functional magnetic resonance imaging
MDA: Malondialdehyde
GSH: Glutathione
BOLD: Blood oxygen level-dependent
MRI: Magnetic resonance imaging
CRFs: Paper case report forms
